### Outcome measures

The primary outcome measure is the inpatient length of stay. This will be recorded in 2 ways: 1) the actual duration of inpatient stay will be determined from the computerised database of patient admission; 2) Given that the length of stay can be affected by many administrative and social factors unrelated to the condition of the child, we will record and report also the time until the child is ready for discharge using objective criteria. An infant will be considered ready for discharge if he/she has not received supplemental oxygen for 12 hours, has had stable respiratory status for 4 hours (including slight or nil recession) and is feeding adequately.

The secondary outcome measures are the incidence and type of complications of hydration therapy (complications will include any adverse event related to the method of hydration, including but not limited to electrolyte abnormalities, IV line/NGT needing replacement, infection, thrombosis of the IV site, trauma to the nose from the NGT, pulmonary aspiration, extravasation of IV fluid); the duration of therapy; parental satisfaction (measured daily) and an economic appraisal of each intervention.

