Nasogastric fluid replacement (NGR) is effective and has few complications. It provides the physiological benefit of enteral hydration, which allows the body to absorb the required amounts of water and solute. In children with dehydration due to gastroenteritis, NGR is the treatment of choice as it provides faster recovery, shorter hospital stay and lowers the cost compared to IV fluid replacement (IVR) [12,13]. A nasogastric tube (NGT) can often be inserted more easily than an IV catheter, especially in infants with poor peripheral circulation due to reduced oral intake. However, concerns have been raised regarding the use of nasogastric tubes (NGT) in infants with bronchiolitis. There may be an increased risk of aspiration in patients with bronchiolitis [14]. The partial obstruction of the upper airway may compromise respiratory function, [15-18] with some studies showing up to a 50% increase in the work of breathing [16]. However these studies have been mostly in young or preterm infants and the ability to extrapolate these findings to older infants with bronchiolitis is questionable.

Intravenous fluid replacement (IVR) is commonly used in bronchiolitis[1]. However, accidental water intoxication and electrolyte imbalances are potential complications [10]. Up to 30% of children admitted with bronchiolitis have been shown to have some degree of hyponatraemia requiring vigilance with IV fluid administration[19,20]. It has also been postulated that delaying enteral nutrition will cause delay in recovery due to loss of nutritional status, and that the persisting hunger may make the children more irritable.

Kennedy et al (2005)[21] reviewed the evidence for fluid replacement in children with bronchiolitis. The authors report a wide variation in practice, with use of NGR in many units. They conclude that "there is no good quality evidence for or against the use of NGR in infants with bronchiolitis. A randomised controlled trial is needed." Vogel (2003) [22] described the management of bronchiolitis admissions in New Zealand hospitals in 1998. There was a large variation in management between hospitals, with between 6% and 64% of children needing fluid replacement therapy receiving NGR.

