#### Laboratory investigations

Electrolytes, urea and creatinine, and glucose levels will be measured when inserting the IV line. Electrolytes will be repeated 6-8 hours after commencement of therapy in the intravenous therapy group (as an accepted standard in IV fluid management); and daily thereafter. Blood sampling may be by draw back on IV cannulae with discarding of 2 mls of blood or alternatively sampling by IV access or capillary blood sample at the discretion of physician managing patient. All testing of electrolyte levels in patients with iv fluids and non testing in patients with NG fluids are in line with current local recommended practice and represent standard care at the participating hospitals [23]. No additional blood tests will taken for the purpose of this trial.

Other investigations will be at the discretion of the managing physician.

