### Sample size, power and statistical methods

The minimal clinically significant difference in length of hospital stay was thought to be greater than or equal to 12 hours. In order to perform the sample size calculation we determined mean duration of hospital stay and standard deviation (sd) from two available sets of admitted patients with bronchiolitis. Mean (sd) length of inpatient stay in a retrospective review of 36 patients admitted with bronchiolitis and requiring fluid replacement was 84 (49) hours. For the patients who were enrolled and randomised in the pilot study, mean (sd) duration of admission was 98 (70) hours, suggesting that patients who enter the study may have more severe illness.

Recruiting a total of 750 subjects (375 per arm) will give 80% power to detect an effect size of 0.2 (a small effect) using a two group t-test with a 0.05 two-sided significance level. That is a difference of 0.2 standard deviations between the mean length of stay in the 2 groups. If the sd is 70 hours (as in the pilot of the protocol), the study will be able to detect a difference between the groups of 14 hours; if the sd is 50 hours (as in the retrospective review), the study will be able to detect a difference of just over 8 hours. Thus, this study is powered to detect a difference in duration of admission of 14 hours, and possibly much less.

For the secondary outcomes, using this sample size, and knowing that approximately 30% of all intravenous cannulae have been shown to have complications,[25-28] gives 80% power to detect a 30% change in complications (from 30% to 20%) with a 0.05 significance level.

Analysis will be by intention to treat. Data will be analysed descriptively and statistically using the STATA data analysis program. Since this is a RCT and 2 of the outcome measures are measured on a continuous scale (duration of inpatient stay or hours of therapy), t-tests will be used to compare the 2 groups. If necessary due to skewed data, the data will be log-transformed. Data on parental satisfaction and complications will be treated as categorical and a Chi-squared test will be used.

No interim analysis of the data is planned.

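### Electrolyte abnormalities count as a complication but are routinely looked for only in the IV arm, which biases the complication comparison against IV

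*Protocol article*

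**What the plan says.** The Outcome measures section makes the incidence and type of complications of hydration therapy a secondary outcome, and electrolyte abnormalities come first in its list of examples: "complications will include any adverse event related to the method of hydration, including but not limited to electrolyte abnormalities". Under Sample size, power and statistical methods, complications are treated as categorical and compared by chi-squared test, by intention to treat. That section also gives a power statement for a change in complications from 30% to 20%.

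The Laboratory investigations section sets out who is tested:

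- **At the start:** "Electrolytes, urea and creatinine, and glucose levels will be measured when inserting the IV line".
- **During treatment:** "Electrolytes will be repeated 6-8 hours after commencement of therapy in the intravenous therapy group", and daily after that.
- **NG arm:** the section says that testing with IV fluids and "non testing in patients with NG fluids are in line with current local recommended practice".
- **Trial-specific tests:** "No additional blood tests will taken for the purpose of this trial".
- **Anything else:** "Other investigations will be at the discretion of the managing physician".

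The article gives no rule for handling the unequal testing. Its Limitations section discusses the lack of blinding but not this difference in ascertainment.

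**The concern.** One arm is tested repeatedly for a listed outcome event and the other is, by plan, not routinely tested. An abnormality without clinical signs is recorded in an IV infant and missed in most NG infants, even if it is equally frequent in both. The chi-squared test cannot tell a real excess from an excess created by testing.

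What is at stake is the trial's comparative safety result. NG could appear to have fewer complications because NG infants were not tested. A true IV advantage in other complications could also be hidden. The Background names electrolyte imbalance as a potential complication of IV fluids, so readers will look for exactly this comparison.

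**Working it through.** **The plan's own figure.** The plan states 80% power for a 30% change in complications, from 30% to 20%, at the 0.05 level; "Recruiting a total of 750 subjects (375 per arm) will give 80% power" fixes the arm size at 375. I used the pooled two-proportion test, two-sided:

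power = Φ( [d − 1.96·√(2p̄(1−p̄)/n)] / √([p₁(1−p₁)+p₂(1−p₂)]/n) ).

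- 30% versus 21% (a 30% relative change): d = 0.09, p̄ = 0.255. The numerator is 0.09 − 1.96 × 0.0318 = 0.0276 and the denominator is 0.0317, which gives 80.8%.
- 30% versus 20% read literally: 88.7%.

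The stated 80% therefore reproduces on the relative-change reading and is conservative on the literal one.

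**Model for the testing effect.** Let

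- b = risk of any other complication, equal in both arms;
- e = true risk of a countable electrolyte abnormality, equal in both arms and independent of b;
- s = share of NG abnormalities that are detected, with all detected in IV.

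Then P(IV) = 1 − (1−b)(1−e) and P(NG) = 1 − (1−b)(1−e·s). The artefact is their difference, (1−b)·e·(1−s). It is zero when s = 1.

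**Inputs.** n = 375 per arm is from the article. For b I used 30%, the article's planning rate, and 20%, its lower rate. The article gives neither e nor s. I assumed e = 1%, 5% and 10%, and s = 0 and 0.5.

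**Worked case.** With b = 30%, e = 10%, s = 0: P(IV) = 1 − 0.70 × 0.90 = 37% and P(NG) = 30%. With p̄ = 0.335, the numerator is 0.07 − 1.96 × 0.0345 = 0.0024 and the denominator is 0.0344. Rejection probability is about 53%, although true risks are equal.

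| b | e | s | IV | NG | Artefact (points) | Chi-squared rejection |
|---|---|---|---|---|---|---|
| 20% | 1% | 0 | 20.8% | 20.0% | 0.8 | 5.8% |
| 30% | 1% | 0 | 30.7% | 30.0% | 0.7 | 5.5% |
| 20% | 5% | 0 | 24.0% | 20.0% | 4.0 | 26% |
| 30% | 5% | 0 | 33.5% | 30.0% | 3.5 | 18% |
| 20% | 10% | 0 | 28.0% | 20.0% | 8.0 | 73% |
| 30% | 10% | 0 | 37.0% | 30.0% | 7.0 | 53% |
| 20% | 1% | 0.5 | 20.8% | 20.4% | 0.4 | 5.2% |
| 30% | 1% | 0.5 | 30.7% | 30.35% | 0.35 | 5.1% |
| 20% | 5% | 0.5 | 24.0% | 22.0% | 2.0 | 10% |
| 30% | 5% | 0.5 | 33.5% | 31.75% | 1.75 | 8% |
| 20% | 10% | 0.5 | 28.0% | 24.0% | 4.0 | 24% |
| 30% | 10% | 0.5 | 37.0% | 33.5% | 3.5 | 17% |

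The nominal rate is 5%.

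**Masking.** Suppose other complications are truly 20% in IV and 30% in NG. If e = 10% is detected only in IV, the IV rate becomes 1 − 0.80 × 0.90 = 28%, compared with 30% in NG. Rejection probability falls from 89% to about 9%.

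**The case against.** Several points on the other side stand.

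**Pre-treatment abnormalities.** The definition covers only events related to the method of hydration. An abnormality in the sample taken at IV insertion precedes the fluid and, on that wording, need not count. A reader might go further and take the Background statement, "Up to 30% of children admitted with bronchiolitis have been shown to have some degree of hyponatraemia", as the rate to be counted, which would make a false positive almost certain. The article does not support this. The figure is an upper bound, for any degree of hyponatraemia, in admitted children generally. It is not a rate of events caused by hydration. The asymmetry survives without it, because the repeat samples at 6-8 hours and daily are also IV-only.

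**Some NG infants will be tested.** The physician may order tests, and an NG infant who changes to IV would have blood taken when the line goes in. This is why the table includes s = 0.5. It shrinks the bias but does not remove it.

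**The composite is not spelled out.** The outcome names both incidence and type. If complications are compared by type, device failure, trauma and aspiration are not contaminated. The electrolyte category would then carry the whole bias, visibly.

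**The power statement.** Its 30% comes from complications of IV cannulae. The article does not say that laboratory findings enter that rate, so one cannot claim that the powered comparison was built on them.

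**Testing is standard care, and IV fluids may really disturb electrolytes.** Both may be true. The first explains the schedule without making the comparison fair. The second is what this design cannot show, since the untested arm supplies no comparison.

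**Conclusion.** The point holds as a should-fix. As written, the plan counts laboratory-detected electrolyte abnormalities as complications, tests for them routinely in one arm only, and compares the arms. The direction, against IV, follows from the text.

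The size does not follow from the text. It rests on the assumed e and s, on independence, and on equal true risk. Under those assumptions the effect is negligible if countable abnormalities occur in about 1% of infants. At 5-10% it is material: 18-73% false positives with no NG detection, and 8-24% with half detected.

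A reader might infer that the main result is compromised. It is not: this counting rule does not enter length of stay. A reader might also infer that complication costs need the same correction. The Economic evaluation section costs tests, procedures and complications that are actually incurred. If IV infants are tested and the results acted on, those costs belong to the IV strategy.

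**What to change.** Change the outcome definition and analysis wording as follows.

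- Base the between-arm complication comparison on events that can be seen equally in both arms: device replacement, site or nose injury, infection, thrombosis, extravasation, aspiration, and clinically manifest electrolyte events such as seizure.
- Report laboratory-detected electrolyte abnormalities separately and descriptively, with the number of infants tested in each arm. Distinguish those on the sample at IV insertion from those on later samples.
- Leave the costing unchanged.

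No extra blood tests and no change in care are needed. The Discussion reports that over 190 infants had already been randomised, so the rule should be written down before complications are compared by arm.

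The cost is that silent electrolyte disturbance, a possible harm of IV fluids, leaves the comparative rate and appears only descriptively.

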**Methods/Design:**

A prospective randomised multi-centre trial in Australia and New Zealand where children between 2 and 12 months of age with bronchiolitis, needing non oral fluid replacement, are randomised to receive either intravenous (IV) or nasogastric (NG) rehydration.

750 patients admitted to participating hospitals will be recruited, and will be followed daily during the admission and by telephone 1 week after discharge. Patients with chronic respiratory, cardiac, or neurological disease; choanal atresia; needing IV fluid resuscitation; needing an IV for other reasons, and those requiring CPAP or ventilation are excluded.

The primary endpoint is duration of hospital admission. Secondary outcomes are complications, need for ICU admission, parental satisfaction, and an economic evaluation. Results will be analysed using t-test for continuous data, and chi squared for categorical data. Non parametric data will be log transformed.

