### Study Design and setting

This study is an open randomised trial comparing two interventions. This study will take place in 6 paediatric emergency departments and inpatient wards in Australia and New Zealand.

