#### Clinical observations from nursing records

SpO_2_, respiratory rate, respiratory effort, and heart rate will be measured at enrolment, at hourly intervals for the first 2 hours then 2 hourly. These will allow comparison of groups by severity of disease at enrolment, and ensure any clinically relevant complications are captured.

Oxygen administered (L/min for nasal cannulae or %O_2 _for head box) will be documented for each shift. The times oxygen is commenced and ceased will be documented. This will allow accurate capture of the duration of oxygen therapy. Type, route and volume of fluid administered will be recorded, with hourly, shift, and daily totals. This allows assessment of fluid requirements and cross referencing volumes of fluid infused. Hydration status of the patients will be measured using urine output (with shift and daily totals) and weight (measured at the time of admission, and then daily).

Complications recorded will include: episodes of apnoea and bradycardia (lasting more than 20 seconds); all episodes where the SpO_2 _was recorded at < 90%; and the need for replacement of, or problems with the IV cannula or NGT.

The need for and duration of ICU admission will be documented. Duration of hospital admission will be documented and checked by calculation from the hospital admissions and discharge system.

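### The abstract, the nursing-record section and the outcome section disagree on the safety outcomes, and a relatedness condition in an open trial may count respiratory events unequally by arm

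*Protocol article*

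**What the plan says.** Three places in the protocol article describe the safety outcomes.

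- **Outcome measures.** Complications of hydration therapy are a secondary outcome, and the entry condition is relatedness: "complications will include any adverse event related to the method of hydration". The list that follows is open-ended and ends with "trauma to the nose from the NGT, pulmonary aspiration, extravasation of IV fluid". Apnoea, bradycardia, low SpO2 and ICU admission are not named.
- **Clinical observations from nursing records.** Here the term has no relatedness condition: "Complications recorded will include: episodes of apnoea and bradycardia (lasting more than 20 seconds"; the same sentence adds every recorded SpO2 under 90% and problems with the cannula or tube. On intensive care, "The need for and duration of ICU admission will be documented".
- **Abstract, Methods/Design.** "Secondary outcomes are complications, need for ICU admission, parental satisfaction, and an economic evaluation".

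The Study Design section states that "This study is an open randomised trial comparing two interventions". The Background gives aspiration and airway compromise as the concerns about nasogastric tubes: "The partial obstruction of the upper airway may compromise respiratory function". The section on sample size and statistical methods compares complications by a chi-squared test under intention to treat, without saying which of the two descriptions of a complication applies.

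**The concern.** A reader cannot tell from the article whether a desaturation in a randomised infant counts towards the complication outcome. Under the nursing-record description it does. Under the outcome definition it does only if it is held to be related to the method of hydration.

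That condition does not act evenly. Apnoea or desaturation can come from bronchiolitis itself. With a tube in the nose, someone who knows the allocation can plausibly link the event to the tube; with a cannula in the hand, hardly anyone would. Randomisation protects a comparison of all events by arm. It does not protect a comparison of the events that someone has attributed. This asymmetry would arise even if clinicians had no preference between the methods, so the argument under Limitations that each method was used about half the time beforehand does not remove it.

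The error can go either way. Readier attribution in the nasogastric arm can produce a harm that is not there. If few events are attributed in either arm, a real respiratory harm can be diluted or lost. ICU admission raises a different issue: it is a secondary outcome in one list and absent from the other.

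**Working it through.** **1. The three lists side by side**

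| Event | Abstract | Nursing records | Outcome measures |
|---|---|---|---|
| Apnoea, bradycardia, SpO2 < 90% | not named | complication, no relatedness condition | not named; could enter the open list if related |
| Pulmonary aspiration | not named | not named | named, under the relatedness condition |
| Line or tube replacement | not named | complication | named |
| ICU admission | secondary outcome | documented | not named |

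**2. The plan's own figure for complications**

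Inputs from the sample-size section: 375 per arm, 30% in one arm, a 30% change described as 30% to 20%, alpha 0.05 (taken as two-sided), stated power 80%. Normal approximation, with p̄ the mean of the two rates:

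power = Φ[(|p1 − p2| − 1.96·s0) / s1], where s0 = √(2·p̄(1 − p̄)/n) and s1 = √(p1(1 − p1)/n + p2(1 − p2)/n).

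- 30% v 21% (a 30% relative fall): 80.8%, which reproduces the stated 80%.
- 30% v 20%: 88.7%, so 80% is conservative.

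The 30% comes from intravenous cannula complications. The article gives no rate for respiratory events, so the event rates and attribution shares below are assumptions.

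**3. Attributed respiratory events compared alone**

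Equal true rates in both arms; counted rate = true rate × share attributed. The result is the exact probability that an uncorrected chi-squared test at two-sided 0.05 rejects, n = 375 per arm. An unbiased comparison would give about 5%.

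| True rate, both arms | Share attributed, NG v IV | Counted, NG v IV | Falsely significant |
|---|---|---|---|
| 20% | 50% v 10% | 10% v 2% | 99.8% |
| 20% | 30% v 15% | 6% v 3% | 51% |
| 10% | 30% v 15% | 3% v 1.5% | 27% |

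**4. The same events pooled into one complication outcome**

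Assume 30% of infants in both arms have some other complication, independent of the attributed respiratory events. The pooled rate is 1 − 0.70 × (1 − attributed rate).

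| Attributed | Pooled, NG v IV | Falsely significant |
|---|---|---|
| 10% v 2% | 1 − 0.70 × 0.90 = 37.0% v 1 − 0.70 × 0.98 = 31.4% | 37% |
| 6% v 3% | 1 − 0.70 × 0.94 = 34.2% v 1 − 0.70 × 0.97 = 32.1% | 9% |
| 3% v 1.5% | 1 − 0.70 × 0.97 = 32.1% v 1 − 0.70 × 0.985 = 31.05% | 6% |

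**5. The opposite error**

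Take a true difference of 30% v 20% and an attributed share that is the same in both arms. Power falls from 88.7% with all events counted to 54% with half attributed (15% v 10%) and 34% with three in ten attributed (9% v 6%).

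**6. What an attribution-free comparison can detect**

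The Background gives 7.4% ICU admission among all Victorian bronchiolitis admissions in 2006, which is not the trial population. From that base, 375 per arm has 80% power for a rise to 13.7% or a fall to 2.9%. For respiratory events, assumed base rates of 10% and 20% allow detection of rises to 17.0% and 28.8%.

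**The case against.** The best defence reads the sections together: the nursing-record section lists what is recorded as a complication, and the outcome section gives an open list of examples. On that reading nothing is excluded. Several parts of this stand.

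- A reader might infer that the outcome definition shuts respiratory events out. It does not: the list is open-ended and includes pulmonary aspiration, one of the Background's two concerns. What remains is that the open list still carries the relatedness condition and the nursing-record description does not.
- A reader might infer that unblinded staff are instructed to judge relatedness event by event. The article does not say so for this outcome. It says that the trial is open, that the investigator evaluates adverse experiences, and that clinician or researcher bias is possible. The rest is inference, and adjudication rules may be in the full protocol or analysis plan, which are not shown.
- Most listed device items, such as replacement, extravasation and nasal trauma, are identified by their occurrence or by the device, so attribution matters little for them.
- ICU admission needs no relatedness judgement. Its absence from the outcome section is a mismatch with the abstract, not evidence of attribution bias.
- Respiratory harm is not unmeasured. Oxygen use and respiratory stability enter the readiness-for-discharge measure, and an independent committee reviews outcomes and complications annually.

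The defence does not settle which description the chi-squared test will use. The two give different counts for the events that matter most to the tube question.

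**Conclusion.** The point holds as an inconsistency in the outcome definitions, one branch of which is open to differential attribution. It concerns secondary outcomes, but these carry the trial's main comparative safety evidence, so it should be settled before any comparison by arm.

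The size cannot be fixed from the document. The near-certain false signal of 99.8% needs three things at once: a 20% event rate, a five-fold gap in attribution, and respiratory events analysed on their own. It should not be read as the expected behaviour of the pooled complication outcome, where the same assumptions give about 37% and the two milder sets give about 9% and 6%, the last close to nominal. The pooled figures in turn assume 30% of other complications in both arms, although the article cites that rate for cannulae only, and independence between the two kinds of event.

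**What to change.** Reconcile the abstract, the nursing-record section and Outcome measures. In Outcome measures, name two further secondary outcomes, compared by intention to treat in all randomised infants and regardless of attribution:

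- (a) any apnoea, bradycardia or SpO2 below 90% after randomisation, as already defined for the nursing records;
- (b) ICU admission, as in the abstract.

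Report device complications separately, by type and by occurrence. If a judgement of relatedness is kept for any event, present it as a description beside these comparisons and do not use it as the condition for being counted.

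The cost is a change of wording and two more secondary chi-squared tests. The article already provides for collecting the data, so no further infants or procedures are needed. The drawbacks are that events from the disease itself add background in both arms, that power for rare events is limited, and that two more secondary comparisons need cautious reading. Recruitment is under way, with over 190 infants randomised, so the change should be dated and made without sight of results by arm.
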